### Body composition assessments

Body composition (total lean mass, fat mass and fat per cent) will be assessed using bioelectrical impedance in both centres (Tanita BC-418 in NDBC and Bodystat-2500 in VBC). In VBC, a DXA examination will be additionally performed (Hologic Discovery) to obtain total and depot specific lean mass, fat mass and total fat percentage. DXA body composition analysis was assessed among NDBC participants in 2009^65^ and will not be re-examined in IndEcho.

A copy of the full protocol can be obtained from the corresponding author.

### Sample size and analysis

We will target the surviving cohort members (1508 from NDBC and 2156 from VBC) who participated in follow-ups between 1998 and 2002. From initial tracing in early 2016, a total of 3500 individuals were recontacted, among whom we expect approximately 1250 in Delhi and 1750 in Vellore to participate (total 3000) in the current protocol.

Exposures in early life will include weight and length at birth: weight, height and BMI and independent conditional weight and height estimates of growth during infancy, childhood and adolescence, as previously described.^48^ Because early growth measurements were measured at different time points and at slightly different ages in both cohorts, and owing to the skewness of BMI, the data will be transformed into SD scores using the lambda-mu-sigma (LMS) method.^66^ The main analysis will use all available data at each time point; it will also be repeated using the subset of participants having data for all time points (birth, infant, childhood and adolescent measurements). Exposures in young adult life will include lifestyle characteristics (diet, physical activity, smoking and alcohol consumption, SES, urban/rural residence and history of rural–urban migration (Vellore only)), anthropometry, lean and fat mass measured by DXA and bioimpedance, metabolic risk markers (plasma glucose, insulin and lipids) and categorical abnormalities as defined above.

We will check the distributions of all variables and perform appropriate transformations. We will explore relationships between LV wall thickness and mass (as continuous variables) with current body size and make appropriate adjustments, including the conventional adjustment for body surface area and height.^60^ We will create categorical variables to represent LVH and ventricular dysfunction based on standard cut-offs for LV mass as described above.^61^ We will examine associations of early life and young adult exposures with outcomes, using linear and logistic regression as appropriate, with and without adjustment for potential confounders and covariates (including age, sex, history of migration, current body size and composition). We will also use the conditional growth modelling approach to relate growth in BMI and height during discrete age periods with adult outcomes.^67 68^ We will explore interactions between early life and young adult exposures and between early life exposures and current measures, using product terms. The role of young adult lifestyle and CVD risk markers as mediators of associations between early-life exposures and outcomes will also be examined. To test the representativeness of the IndEcho participants and assess the risk of bias, we will compare their early growth variables (birth length, birth weight and height, weight and BMI in infancy, childhood and early adulthood) with members of the original cohorts who did not participate as we have done previously (table 2). Since all analyses in the IndEcho study will be ‘internal’ (within the sample of participants) bias will occur only if the associations between early growth and adult outcomes differ between those who participate in IndEcho and those who were not studied. We cannot think of a mechanism by which such differences could occur. We will examine the data from men and women, from Delhi and Vellore and (in Vellore) among rural and urban participants separately and assess heterogeneity of associations and scope for pooling.

**Table 2 T2:** Comparison of early growth measurements of studied and not-studied participants during phase 1 adult follow-up

Measurement	New Delhi birth cohort				Vellore birth cohort			
	Male		Female		Male		Female	
	Studied as adult		Studied as adult		Studied as adult		Studied as adult	
	Yes	No	Yes	No	Yes	No	Yes	No
Birth								
n	808	2642	569	2497	1159	1712	1058	1741
Weight (kg)	2.89±0.44	2.86±0.46	2.79±0.38	2.78±0.44	2.85±0.53	2.83±0.61	2.78±0.5	2.76±0.54
Length (cm)	48.8±2.2	48.7±2.4	48.3±1.9	48.1±2.2	48.3±3.0	47.8±4.6	47.8±3.0	47.3±4.3
Ponderal index (kg/m^3^)	24.8±2.6	24.7±2.9	24.7±2.5	24.9±2.9	25.7±7.6	25.6±7.3	25.7±6.6	25.9±7.3
Gestation (week)	39.2±2.2	39.2±2.3	39.6±2.0	39.6±2.2	38.2±2.8	38.1±2.9	38.3±2.8	38.4±2.8
Infancy (3 months)								
n	660	2140	503	2105	845	1011	791	1108
Weight (kg)	5.50±0.7	5.46±0.8	4.96±0.7	4.99±0.7	4.28±0.8	4.17±0.9	4.04±0.7	3.91±0.8
Height (cm)	59.6±2.4	59.5±2.7	58.0±2.4	58.1±2.5	55.2±3.1	55.1±3.6	54.3±2.9	54.2±3.2
BMI (kg/m^2^)	15.4±1.5	15.4±1.6	14.7±1.6	14.7±1.6	14.1±1.9	13.6±2.2	13.6±1.7	13.12±1.92
Childhood (6 years)								
n	837	1092	608	1219	1001	601	933	645
Weight (kg)	17.2±2.2	17.3±2.3	16.4±2.0	16.5±2.2	15.8±4.4	15.5±4.4	15.4±4.3	15.4±4.2
Height (cm)	108.4±5.2	108.9±5.5	107.0±5.1	107.2±5.5	102.4±18.7	100.1±26.4	100.6±19.7	100.6±23.5
BMI (kg/m^2^)	14.6±1.1	14.5±1.1	14.3±1.1	14.3±1.2	15.4±4.4	15.3±4.1	15.6±4.8	15.2±4.11
Adolescence (15 years)								
n	616	435	481	592	775	467	727	508
Weight (kg)	44.6±9.2	45.8±9.6	44.6±7.8	44.2±7.5	27.7±5.8	27.5±6.3	28±5.37	28.5±6.1
Height (cm)	159.2±8.7	160.2±8.4	153.2±5.7	153.3±6.2	136.5±9.9	137.1±13.6	135.3±8.0	136.5±9.9
BMI (kg/m^2^)	17.5±2.5	17.7±2.7	18.9±3.0	18.8±2.7	14.7±1.4	14.6±1.6	15.2±1.9	15.2±1.8
Adulthood								
n	886	—	640	—	1159	—	1053	
Age (years)	29.2±1.3	—	29.2±1.4	—	27.9±1.1	—	28.3±1.2	—
Weight (kg)	71.8±14.0	—	59.2±13.4	—	57.4±11.4	—	49.3±10.6	—
Height (cm)	169.7±6.4	—	154.9±5.7	—	166.4±6.7	—	153.8±6.0	—
BMI (kg/m^2^)	24.9±4.3	—	24.6±5.1	—	20.7±3.5	—	20.8±4.1	—

BMI, body mass index.

Using tests at 5% significance and a total sample size of 3000, we will have 80% power to detect an association of 0.05 SDs of a continuous outcome (eg, LV mass) per SD change in a continuous predictor (eg, birth weight or conditional weight gain in infancy). For the Vellore cohort alone (based on n=1750), this figure is 0.07 SDs and for the Delhi cohort alone (based on n=1250), it is 0.08 SDs. These figures compare favourably with the association shown between infant weight and adult LV mass in the Hertfordshire cohort (0.17 SD per SD change in infant weight).^26^ For a binary outcome such as LV diastolic dysfunction (Grades 1 and 2), assuming 10% prevalence and a test at 5% significance level, we will have 80% power to detect an association of 0.17 log odds per SD change in a continuous predictor, equivalent to an OR of 1.19 (Vellore 1.25, Delhi 1.30).

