South Asian newborns have a low mean birth weight (2.6–2.7 kg) compared with white Caucasian babies^21 23^ and frequently show suboptimal growth and weight gain during infancy.^24^ Low birth and infant weight are risk factors for CVD mortality in adult life and have also been linked to a high risk of hypertension and T2DM.^25 26^ It has been suggested that these associations reflect ‘developmental programming’, permanent structural and functional deficits in key metabolic organs (eg, liver, pancreas and kidneys) and tissues (eg, muscle) resulting from impaired nutrition during fetal and early childhood development.^27^ Studies in India have linked lower birth weight to higher blood pressure, serum lipids and abnormal glucose tolerance in children and adults.^28–30^ The risks associated with lower birth weight appear to be increased on subsequent exposure to greater child or adult weight gain. Upward crossing of BMI centiles in childhood and adolescence is associated with increases in several CVD risk factors such as higher adult cholesterol, triglyceride and proinflammatory marker concentrations and with an increased risk of obesity, impaired glucose tolerance or T2DM (figure 1), hypertension and metabolic syndrome.^29 31^

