## Discussion

To the best of our knowledge, IndEcho will be the first study among South Asians to provide data linking birth size and childhood growth, as well as prior measures of CVD risk markers and lifestyle factors such as physical activity and smoking in young adulthood, with cardiac structure and function and in middle age. It will provide an opportunity to study interactions between early life, young adult and concurrent risk factors in relation to myocardial outcomes.

The main strengths of the study are that it includes participants from two large Indian birth cohorts that have serial childhood growth data, measured prospectively by trained research staff and risk factors for CVD (including lifestyle risk factors) assessed 16–20 years ago. Harmonised methods will be used in both cohorts. The participants represent north and south Indian populations, different socioeconomic strata and rural and urban settings. Because we have serial measures of SES, collected using identical methods, IndEcho provides an opportunity to assess the impact of economic transition on cardiac health in Indians. At this age, we will detect subclinical cardiac disease in an apparently healthy population where obesity, hypertension and T2DM are escalating. In 1998–2002 at age 26–32 years, the prevalence of obesity (BMI >30 kg/m^2^), hypertension (systolic >140 mm Hg or diastolic >90 mm Hg or on treatment for hypertension) and diabetes (WHO criteria) was 11%, 8% and 4%, respectively, in NDBC^29^ and 2%, 3% and 3% in VBC.^31^ Approximately 5 years later, at 34–39 years, the prevalence had more than doubled in NDBC (23%, 26% and 9%).^45^ In the 2013–2014 VBC follow-up, the equivalent data (16%, 20% and 17%) showed a more than fivefold increase in prevalence in just over a decade (unpublished data).

Like all birth cohorts of this age, an important limitation is loss to follow-up, mainly due to deaths in childhood and migration out of the original study area. However, current cohort members were similar in early life to the rest of the original cohorts (table 2).^29 48^ To create bias, the relationship between the predictors (eg, birth weight or young adult diabetes) and outcomes (eg, LV mass) would have to differ between those studied and not studied. Another limitation is that, because this is a field-based study, echocardiography will be used rather than cardiac MRI which is the current gold standard method for measuring myocardial structure.

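### The plan rules out a mechanism for selection bias that its own background supplies, and its size-only comparison could not detect such bias

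*Protocol article*

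**What the plan says.** The Sample size and analysis section argues that, because all analyses are internal to the sample, the condition for bias is narrow: "bias will occur only if the associations between early growth and adult outcomes differ between those who participate in IndEcho and those who were not" (that is, not examined). It then adds: "We cannot think of a mechanism by which such differences could occur". The Discussion repeats the condition.

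The check offered for representativeness and risk of bias is a comparison of body size: "we will compare their early growth variables (birth length, birth weight and height, weight and BMI in infancy, childhood and early adulthood". Table 2 is given as the model. Its title is "Comparison of early growth measurements of studied and not-studied participants during phase 1 adult follow-up", so it describes entry to the 1998–2002 study, not to IndEcho. Citing Table 2, the Discussion concludes that "current cohort members were similar in early life to the rest of the original cohorts". It attributes the attrition to "loss to follow-up, mainly due to deaths in childhood and migration out of the original study area".

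Elsewhere the article says: "Low birth and infant weight are risk factors for CVD mortality in adult life". The same Background section says that LVH raises the later risk of heart failure and death. Hypothesis 4 expects adult risk factors to be more strongly related to LVH, LV dysfunction and cIMT in people who were small at birth or in infancy.

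**The concern.** There are three linked problems.

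1. **The denial conflicts with the background.** If early size and cardiac status both influence who is alive, traceable and willing to attend, selection acts on exposure and outcome together. That is a mechanism by which the association among participants can depart from the one in the full cohort.
2. **The stated condition is not strictly correct.** Participants and non-participants can have nearly the same slope while both differ from the slope in the whole population.
3. **The check is aimed at the wrong quantity.** A difference in mean exposure between groups neither proves nor excludes a distorted exposure–outcome slope.

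At stake is hypothesis 3, which predicts inverse associations with birth and infant weight. The study is powered for associations as small as 0.05 SD per SD, so modest selection effects are not negligible beside the target. As written, a size table with few differences would be read as evidence against bias, which it cannot provide.

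**Working it through.** **Plan's own figure.** Detectable slope = (1.960 + 0.842)/√N. With N = 3000 this is 2.802/54.77 = 0.051, so the stated 0.05 SD per SD reproduces.

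**Table 2, Vellore, studied minus not studied at phase 1.** z = difference/√(s₁²/n₁ + s₂²/n₂). Standardised difference (SMD) = difference/√((s₁² + s₂²)/2).

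| Measure | Studied | Not studied | Difference | z | SMD |
|---|---|---|---|---|---|
| 3-month BMI, men | 14.1 (1.9), n=845 | 13.6 (2.2), n=1011 | +0.50 | 5.25 | 0.243 |
| 3-month BMI, women | 13.6 (1.7), n=791 | 13.12 (1.92), n=1108 | +0.48 | 5.75 | 0.265 |
| 3-month weight, men | 4.28 (0.8) | 4.17 (0.9) | +0.11 kg | 2.79 | 0.129 |
| 3-month weight, women | 4.04 (0.7) | 3.91 (0.8) | +0.13 kg | 3.76 | 0.173 |
| Birth length, men | 48.3 (3.0), n=1159 | 47.8 (4.6), n=1712 | +0.5 cm | 3.52 | 0.129 |
| Birth length, women | 47.8 (3.0), n=1058 | 47.3 (4.3), n=1741 | +0.5 cm | 3.62 | 0.135 |
| Birth weight, men | 2.85 (0.53) | 2.83 (0.61) | +0.02 kg | 0.93 | 0.035 |
| Birth weight, women | 2.78 (0.5) | 2.76 (0.54) | +0.02 kg | 1.00 | 0.038 |

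Delhi shows little. Birth weight and 3-month size do not differ clearly. Birth length differs by +0.2 cm in women (z = 2.20). In men, those studied were shorter at 6 years (108.4 v 108.9 cm, z = −2.04) and lighter at 15 years (44.6 v 45.8 kg, z = −2.03).

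**Participation and deaths.** Expected participation is 3000/(1508 + 2156) = 3000/3664 = 81.9%, leaving about 664 surviving non-participants. Known deaths after phase 1 are 18 + 62 = 80 of 1526 + 2218 = 3744, or 2.1%. Before that, phase 1 reached 1526/8181 = 18.7% of births in Delhi and 2218/10 691 = 20.7% in Vellore.

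**Why the stated condition fails.** Let p be the participating fraction, and Δx and Δy the differences in mean exposure and outcome (SD units) between participants and others. If both groups share the slope b, the whole-population slope is approximately b + p(1−p)·Δx·Δy. The participants' slope is therefore off by about −p(1−p)·Δx·Δy even though the groups agree. If Δy = 0 (selection on exposure alone), the bias is zero whatever Δx is.

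**Illustration.** x and y are standardised, participation is logistic, p = 0.82, and there is no true association. All selection coefficients are assumptions; the documents give none.

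| Log-odds per SD: x, y, product | Δx | Bias in slope |
|---|---|---|
| 0.2, 0, 0 | 0.20 | 0 |
| 0.2, −0.3, 0 | 0.20 | 0.009 |
| 0.3, −0.3, 0 | 0.29 | 0.013 |
| 0.5, −0.5, 0 | 0.47 | 0.03 |
| 0, −0.3, 0.15 | 0.03 | 0.03 |
| 0.1, −0.3, 0.15 | 0.13 | 0.03 |
| 0.1, −0.5, 0.25 | 0.16 | 0.05 |
| 0.5, −0.5, 0.15 | 0.51 | 0.057 |
| 0.1, −0.3, −0.15 | 0.07 | −0.02 |

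Hand check of the third row: 0.82 × 0.18 × 0.29 × 0.29 = 0.012. With a true slope of −0.05 and the second row's selection, the slope is about −0.04 among participants and about −0.04 among non-participants. The groups agree and both are biased. Rows 1 and 5 show that the size comparison is uninformative: an imbalance of 0.20 SD goes with no bias, and one of 0.03 SD with a bias of 0.03.

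**The case against.** A reader might infer more than the documents support, and the case against those stronger readings is good.

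- **Selective survival.** Table 2 does not show it. The table describes inclusion at phase 1 and does not separate death from migration, non-tracing or refusal. Vellore tracing was also limited to the 4092 members with all birth measurements. The deaths the Discussion blames for attrition are in childhood and cannot have followed from midlife LVH. Known adult deaths in the target group are 2.1%.
- **Scale.** It is tempting to set the quarter-SD gap in Vellore infant BMI against the 0.05 design effect and call it five times larger. One is a difference in means and the other a slope; selection on exposure alone leaves the slope unbiased.
- **A hidden inverse association.** The larger biases need an assumed interaction, and reversing its sign reverses the bias. With exposure coefficients matched to Table 2, an outcome coefficient of −0.5 and no interaction, the bias is only about 0.003 for birth weight and 0.017 for Vellore infant BMI.

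The article also lists attrition openly as a limitation. A weighted analysis could sit in the full protocol or analysis plan, so its absence here is not the fault.

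All of this limits the size of the claim. It does not rescue the statement that no mechanism is conceivable, the incorrect condition, or a list of comparison variables confined to body size.

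**Conclusion.** The point holds as a correction to what the article asserts and to what its check can show. The background and hypothesis 4 supply a plausible route to bias, so the denial should not stand. The claim of similarity is not accurate for Vellore 3-month BMI, 3-month weight and birth length; it is fair for Vellore birth weight and broadly fair for Delhi.

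The documents do not establish the size or direction of bias. At 82% participation it is about 0.01–0.03 SD per SD without an interaction and 0.03–0.06 with one, and smaller for exposures that are nearly balanced, such as birth weight. These figures rest on assumed logistic selection and cover only the last stage of loss. Selection in the roughly 80% of births lost before phase 1 cannot be quantified from the article.

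**What to change.** - Delete the no-mechanism sentence. Replace the condition in both places with a statement that bias can arise when participation depends on exposure and on outcome or its determinants, whether or not the two groups' slopes differ.
- Qualify the similarity claim for Vellore infant size and birth length, and say that Table 2 concerns phase 1 and does not distinguish reasons for loss.
- Extend the planned comparison to 1998–2002 blood pressure, glucose, lipids, smoking and SES, alongside the adult BMI already listed. Compare IndEcho participants with the other phase 1 attendees: about 664 surviving non-participants and the 80 known deaths, where measured.
- Add a sensitivity analysis weighted by the inverse probability of participation, using those variables and early growth. State that it corrects only for loss after phase 1, and that earlier loss can be weighted only on early-growth variables.

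The cost is one extended table, one weighted re-run and a few edited sentences, all from data already collected. Weighting widens the intervals slightly.

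### The 80% power figure is applied to infant weight gain at the full 3000, but Vellore's infancy data cover about 74% of adults, so power at 0.05 SD is about 66–71%

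*Protocol article*

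**What the plan says.** All references are to the Protocol article.

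- **Power.** The last paragraph of Sample size and analysis opens with "Using tests at 5% significance and a total sample size of 3000" and claims "80% power to detect an association of 0.05 SDs of a continuous outcome (eg, LV mass) per SD change" of a continuous predictor. The examples of that predictor are given as "eg, birth weight or conditional weight gain in infancy".
- **Cohort figures.** "For the Vellore cohort alone (based on n=1750), this figure is 0.07 SDs"; the Delhi slope is put at 0.08 SD with n = 1250. For a binary outcome with 10% prevalence, the detectable ORs are 1.19 pooled, 1.25 in Vellore and 1.30 in Delhi.
- **Where 3000 comes from.** The same section expects 1250 participants in Delhi and 1750 in Vellore. These are participation targets, with no deduction for missing exposure data.
- **Missing growth data.** The main analysis takes all data available at each time point, and "it will also be repeated using the subset of participants having data for all time points (birth, infant, childhood and adolescent measurements").
- **Availability.** Table 2 has a row headed "Infancy (3 months"), with counts for those studied as adults at phase 1, the group from which IndEcho recruits.
- **Visit schedules.** The VBC section places infancy measurement in the first 3 months. The NDBC section describes 3-monthly measurement to 12 months and 6-monthly after that. Hypothesis 3 defines infancy as the first two years after birth.

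**The concern.** Weight gain in infancy can be computed only for people with an infancy measurement. In an available-case analysis everyone else drops out of that regression. The power paragraph nevertheless gives this predictor the whole expected sample, while the article's own Table 2 shows that part of the recruitment pool lacks the measurement.

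Infant weight is one of the exposures named in hypothesis 3, and the Discussion expects the study to identify periods of early life suited to intervention. That means comparing growth windows, and the windows differ in precision: birth weight is nearly complete and infancy is not. A reader of the power paragraph would credit the infancy analysis with more sensitivity than it will have.

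**Working it through.** **Inputs**

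- Two-sided 5% level (the article does not state sidedness; two-sided is assumed) and 80% power, so z = 1.960 + 0.842 = 2.802.
- Expected participants: 1250 Delhi and 1750 Vellore.
- Adults at phase 1: 1526 Delhi and 2218 Vellore (NDBC and VBC sections).
- 3-month measurement among those adults (Table 2): Delhi 660 + 503 = 1163; Vellore 845 + 791 = 1636.
- Birth measurement among those adults (Table 2): Delhi 808 + 569 = 1377; Vellore 1159 + 1058 = 2217.

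**Formulas**

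- Standardised slope r: power = Φ(atanh(r)·√(n−3) − 1.960).
- Slope detectable with 80% power: tanh(2.802/√(n−3)), close to 2.802/√n.
- Detectable OR per SD at prevalence 0.10: exp(2.802/√(n × 0.10 × 0.90)).

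**Step 1: reproduce the stated figures at full n**

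| | n | Detectable slope (stated) | Detectable OR (stated) |
|---|---|---|---|
| Pooled | 3000 | 0.051 (0.05) | 1.186 (1.19) |
| Vellore | 1750 | 0.067 (0.07) | 1.250 (1.25) |
| Delhi | 1250 | 0.079 (0.08) | 1.302 (1.30) |

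All of them reproduce, and all use the undiminished sample. At exactly 0.05 with n = 3000, power is 78.2%; the stated 80% belongs to the unrounded slope 0.0511.

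**Step 2: availability of infancy data**

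- Vellore: 1636/2218 = 73.8%, so 1750 × 0.738 ≈ 1291. No later infancy visit is described that could replace a missing one.
- Delhi, lower case (3-month visit only): 1163/1526 = 76.2%, so 1250 × 0.762 ≈ 953.
- Delhi, middle case (limited by birth data, which a conditional gain also needs): 1377/1526 = 90.2%, so 1250 × 0.902 ≈ 1128.
- Delhi, upper case (everyone has usable values): 1250.

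**Step 3: pooled power and detectable effects for infancy**

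| Delhi case | Pooled n | Power at 0.05 | Detectable slope | Detectable OR |
|---|---|---|---|---|
| 3-month visit only | 2243 | 65.9% | 0.059 | 1.22 |
| Limited by birth data | 2419 | 69% | 0.057 | 1.21 |
| Everyone | 2541 | 71% | 0.056 | 1.20 |

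Starting from the unrounded 0.0511, the first row gives 68% rather than 66%. If birth and 3-month data in Delhi overlapped as little as Table 2 permits, pooled n would be about 2121 and power 63%; this is an extreme, not an expectation.

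**Step 4: by cohort**

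- Vellore, n ≈ 1291: 71% power at 0.07; detectable slope 0.078; OR 1.30.
- Delhi, n from 953 to 1250: detectable slope from 0.091 down to 0.079; OR from 1.35 down to 1.30. At n ≈ 1128 they are 0.083 and 1.32. At n ≈ 953, power at 0.08 is 70%.

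**Step 5: two comparisons**

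- Birth weight: 1250 × 1377/1526 + 1750 × 2217/2218 ≈ 2877; detectable slope 0.052, which still rounds to 0.05.
- The article's 0.17 SD benchmark: power is above 99.9% pooled, in Vellore alone (n ≈ 1291) and in Delhi alone even at n ≈ 953.

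**The case against.** The strongest reply has four parts.

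1. **Table 2 counts one visit.** A reader might infer that only about three quarters of all participants have any infancy measurement, so that 66% is the power. For Delhi the documents do not support this. Infants there were measured every 3 months to 12 months, and cohort members averaged 23 sets of measurements to age 21. Someone who missed the 3-month visit may well have another usable infancy value. This stands: 76% is a pessimistic figure for Delhi, and 0.09 SD is not established there. It does not rescue the pooled claim, because the Vellore loss remains and power is about 71% even with Delhi complete.

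2. **Nothing is miscalculated.** Every stated figure reproduces at the n given beside it, and part of the apparent fall from 80% is rounding. This also stands. The fault is an unstated assumption of complete exposure data, not faulty arithmetic. Like for like, the fall is from 78% to 66–71% at exactly 0.05 SD.

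3. **The consequence is small.** The sample is every reachable survivor, so no recruitment decision turns on this, and the 0.17 SD benchmark is met with ample power. This stands, and it limits how serious the point is.

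4. **The predictors are only examples, and missing-data detail belongs elsewhere.** The second half is fair: the article need not describe imputation, and its absence is no fault. The first half is weak, because an example chosen to illustrate a power claim should be one for which the claim is true.

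**Conclusion.** The stated 80% power is not delivered for conditional weight gain in infancy, a predictor the article itself names. Power at 0.05 SD is about 66–71%. The slope detectable with 80% power is about 0.056–0.059 SD pooled, 0.078 SD in Vellore, and between 0.08 and 0.09 SD in Delhi depending on how many infancy visits are usable. The corresponding ORs are about 1.20–1.22, 1.30 and 1.30–1.35.

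This rests on two assumptions: that Table 2 availability among phase 1 adults carries over to the IndEcho participants, and that people without an infancy value are left out of that analysis, as the available-case plan implies. The Vellore figure is the firmer one; Delhi is a range.

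It would be wrong to infer that the study is underpowered for its purpose. The favourable comparison with the 0.17 SD benchmark is unaffected, and birth weight keeps its stated 0.05 SD. This is a worthwhile correction, not one on which the study depends.

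**What to change.** In the power paragraph of Sample size and analysis:

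- Limit the figures based on 3000, 1750 and 1250 to predictors available on nearly everyone, such as birth weight.
- State infancy exposures separately: about 0.06 SD pooled and 0.08 SD in Vellore, with ORs of about 1.22 and 1.30. The pooled OR is the cautious end of 1.20–1.22.
- Compute the Delhi infancy figure from the actual number of participants with a birth measurement and any usable infancy measurement. The cohort database should provide that count; Table 2 does not.

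The cost is a short text edit, one count from the Delhi data and slightly less favourable figures. The planned analysis need not change, and the correction does not need imputation.
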